## Abstract

**Background:**

Occupational cancer and acute cardiac events are the leading causes of death among firefighters. Increased exposure to toxicants on the fire ground, such as polycyclic aromatic hydrocarbons, benzene, and per- and poly-fluoroalkyl substances (PFAS), has been linked to certain cancers, cardiovascular disease, accelerated epigenetic aging, and other adverse health effects. PFAS are a major concern because they are persistent, can bioaccumulate, and are present in several firefighting tools. Compared to the general population, firefighters have elevated serum levels of some types of PFAS. A randomized clinical trial in Australian firefighters found that routine blood and plasma donation for 1 year led to decreased serum PFAS levels, although health outcomes were not directly measured in that study.

**Objective:**

In collaboration with fire service leadership in Arizona, the Firefighter Collaborative Research Project (FCRP) was established to evaluate the effectiveness of 3 interventions in a randomized controlled trial design to reduce serum PFAS levels, reduce cancer and cardiovascular risk, and improve overall health and wellness in US firefighters.

**Methods:**

This study aimed to recruit and enroll up to 1500 active firefighters between August 2023 and October 2024. Between August 2023 and October 2024, active firefighters were recruited and randomized into a study arm based on their eligibility, including serum PFOS levels, for the specific arms. The trial arms include (1) blood and plasma donation, (2) zone 2 physical activity, and (3) intermittent fasting. FCRP outcomes include serum PFAS reduction (arm 1), epigenetic age acceleration (all arms), cardiovascular conditioning (arm 2) and cognitive outcomes (all arms), mental health (all arms), and overall disease risk (all arms). Each study arm includes an intervention and a control group. At enrollment and end of the study, participants provide blood and urine samples and complete a comprehensive questionnaire on their occupational and health history, exposures, and lifestyle behaviors. At the end of the study, participants also participated in a cognitive evaluation. Depending on the study arm, participants may additionally complete a cardiopulmonary exercise test at baseline and follow-up, a mid-study survey, and a mid-study blood and urine collection.

**Results:**

Participant activities and data collection will conclude by December 2025.

**Conclusions:**

The FCRP is a randomized controlled trial that aims to test the effectiveness of fire service–selected interventions in reducing serum PFAS levels. Study results will contribute to potential interventions that could be used to reduce serum PFAS levels in firefighters.

**Trial Registration:**

ClinicalTrials.gov NCT05869747; https://clinicaltrials.gov/study/NCT05869747

**International Registered Report Identifier (IRRID):**

DERR1-10.2196/67120

## Introduction

Occupational cancer and acute cardiac events are the leading causes of death among firefighters [1,2]. The firefighting occupation is classified by the International Agency for Research on Cancer as a group 1 carcinogen due to the direct and indirect exposures to hazards on the job [3]. Firefighters have a significantly higher risk of cancer and cancer mortality when compared to the general population, including skin melanoma, other skin cancers, and prostate cancer, with higher mortality for rectal, testicular, brain and nervous system cancers, and non-Hodgkin lymphoma [4,5]. Increased exposure to toxicants on the fire ground, such as polycyclic aromatic hydrocarbons, benzene, and per- and poly-fluoroalkyl substances (PFAS), have been linked to certain cancers, cardiovascular disease, accelerated epigenetic aging, and other adverse health effects [4,6,7].

PFAS are primary toxicants of concern due to their persistence, ability to bioaccumulate, and associated adverse health effects [8]. Firefighters have additional exposure to these chemicals beyond the general population, with significant sources of PFAS exposure on the fire ground including fluorinated class B aqueous film-forming foam and smoke from burning household materials [6]. A study involving 4 municipal US fire departments located in different states and regions of the country found that firefighters had higher levels of several PFAS chemicals in their blood than the general population [9].

In the human body, PFAS accumulates primarily in the liver, kidneys, and blood. Long-chain PFAS, such as perfluoro octane sulfonate (PFOS) and perfluorooctanoic acid (PFOA), have reported half-lives of several years (3.1-7.4 and 2.1-8.5, respectively) [8]. These chemicals bind strongly to albumin, the most abundant protein in plasma [8,10]. Therefore, these chemicals may be removed from the body through blood or plasma donation. An Australian study among firefighters previously demonstrated the effectiveness of blood or plasma donation to lower serum PFAS levels over 12 months, although no health effects were investigated. Findings from the study revealed that plasma donation was more effective than blood donation at reducing the mean serum level of PFOS at 12 months, while serum PFOS did not significantly change in the control group [11]. Plasma donation reduced PFOS levels by approximately 24% (–2.9 ng/mL, 95% CI –3.6 to –2.3 ng/mL), while blood donation reduced PFOS levels by approximately 11% (–1.1 ng/mL, 95% CI –1.5 to –0.7 ng/mL) [11]. Based on the findings from that study and concern for PFAS exposure, Arizona firefighters requested research to replicate the study and additionally investigate health outcomes such as cardiovascular health and epigenetic age acceleration.

Lifestyle and environmental exposures are associated with DNA methylation patterns, a type of epigenetic alteration. DNA methylation affects gene expression by adding a methyl group to 5’—C—phosphate—G—3’ dinucleotides. These DNA methylation patterns can be analyzed to determine epigenetic age or “biological age” through epigenetic clocks. Previous research has found that accelerated epigenetic age can be a risk factor for cancer, cardiovascular and neurological diseases, as well as death from all causes combined [12]. In addition to the physical health impacts, accelerated epigenetic age has been linked to negative mental health impacts [13]. Studies on firefighters have found differential DNA methylation patterns, or accelerated epigenetic age, potentially as a result of fire ground exposure and increased serum PFAS levels [7,14].

Lifestyle interventions, such as physical activity and dietary restriction or intermittent fasting, may be associated with slowed epigenetic aging [12,15,16]. Findings from the Comprehensive Assessment of the Long-term Effects of Reducing Intake of Energy trial revealed that caloric restriction slowed epigenetic aging [17]. Similar findings have been observed in mice [18]. A recent randomized controlled trial tested the effectiveness of a fasting-mimicking diet (low calorie, low protein, plant-based diet) in improving biological age. After 3 cycles, a cycle being a consecutive 5-day period in a month, biological age was reduced by a median of 2.5 years [19].

Zone 2 physical activity, or continuous, moderate aerobic physical activity corresponding to the near lactate threshold (4 mM blood lactate), shows greater benefits than other types of aerobic physical activity for improving cardiovascular risk factors [20,21]. Common examples of this type of activity include brisk walks, light jogs, and cycling for a continuous interval of time. Occupational health clinicians working with the firefighter community also anecdotally noted that zone 2 physical activity confers the greatest benefits for cardiovascular fitness, although this claim has not been formally tested. Both types of lifestyle interventions, intermittent fasting, and zone 2 physical activity, have received interest from the firefighter community.

The Firefighter Collaborative Research Project (FCRP) aims to assess the effectiveness of fire service–selected interventions for improving firefighter health. The target population for recruitment is participants enrolled in the Fire Fighter Cancer Cohort Study (FFCCS), a national framework study that collects information on firefighter exposures and works to improve the health of the fire service [22]. Through this randomized controlled trial, we seek to engage our existing cohort of firefighters to evaluate 3 firefighter-identified lifestyle interventions: blood or plasma donation, zone 2 physical activity, and intermittent fasting. The primary outcomes of the study include epigenetic age acceleration, serum PFAS reduction (blood or plasma arm only), and cardiovascular risk reduction (zone 2 arm only). Based on the previously mentioned associations with accelerated epigenetic age and therefore aging and aging-related diseases, secondary outcomes of this study include mental health, sleep quality, and cognitive functioning [12,13].

## Methods

### Overall Study Design

The FCRP is a community-engaged, randomized controlled trial with the goal of screening 1500 firefighters. The study enrollment period is planned for August 2023-October 2024. Based on eligibility criteria, participants are randomly assigned to regularly donate blood or plasma for 1 year, engage in zone 2 physical activity for 4 months, intermittent fast for 4 months, or serve as a control for the duration of the respective study arm.

We have chosen a community-based approach working with fire service leaders in participating states that are willing to educate firefighters on the importance of the study and encourage participation. Departments designate a liaison who completes training for institutional review board (IRB) approval to distribute study information, coordinate events, and serve as an additional point of contact between researchers and participants. The study team also hosts online informational sessions upon request and actively maintains a study website. Individuals interested in participating in the study are directed to complete a screening survey and to schedule an appointment for an in-person event near them. Both surveys may be accessed through informational materials dispersed by liaisons. Events are hosted regionally, and locations are prioritized based on interest numbers and resources for study activities.

Initially, the state of Arizona was designated as the only state for enrollment for all 3 study arms (blood and plasma donation, intermittent fasting, and zone 2). However, upon interest from other US fire departments, the blood and plasma donation arm of the trial has been expanded to Idaho, California, Washington, Oregon, and Massachusetts. The intermittent fasting and zone 2 arms of the trial will not include non-Arizona fire departments. Given that there are a limited number of volunteer departments with who we have established contacts within these areas, enrollment is focused on career departments. Firefighters of all demographic backgrounds were encouraged to enroll.

### Participants

#### Eligibility Criteria

Individuals interested in participating in the study are directed to complete an online screening survey to assess eligibility. Overall study eligibility criteria include active firefighters enrolled in the FFCCS, with full criteria described in Textbox 1. If participants are not already enrolled in the FFCCS at recruitment, they are given the opportunity to enroll. Individuals currently doing study arm activities at the time of screening are deemed ineligible for participation in the respective study arm. Subjects with conditions that may affect their ability to complete study activities (eg, they do not meet national standard criteria for blood or plasma donation, or have an injury preventing physical activity) are also deemed ineligible for participation in the respective study arm. Individuals who are deemed ineligible for all study arms are thereby ineligible for participation in the overall study. Specific inclusion criteria are detailed in Textbox 1.

Inclusion and exclusion criteria for the Firefighter Collaborative Research Study (FCRP).
**Inclusion Criteria**
Active firefighter (including emergency medical responder and all firefighter subgroups) with either a volunteer or career statusIndividual plans to remain in active service with their current agency for the next 2 years (not planning to retire or resign)18 years of age and olderFluently speak and write in EnglishAll genders, races, and ethnicitiesEnrolled in the Fire Fighter Cancer Cohort Study before enrolling in the FCRPComplete a signed and dated informed consent document that indicates the participant has been informed of all aspects of the study before enrollment.Agree to avoid participating in FCRP intervention activities outside of their assigned intervention group for the duration of the study.Able to comply with scheduled visits, laboratory tests, and other study proceduresBMI ≥17.5 kg/m^2^ and weighing more than 115 pounds
**Exclusion Criteria**
OverallNot able to fluently speak or write in EnglishYounger than 18 yearsCurrently a tobacco smoker or vaping (eg, >2 cigarettes or cigars, or incidents of vaping in the past month)Those with planned travel or extended leave (eg, >6 weeks) that would prevent their ability to participate in other interventionsThose who are pregnant or become pregnant during study, breastfeeding, or have given birth within the past yearThose with a history or diagnosis of any significant metabolic, hematologic, pulmonary, cardiovascular, gastrointestinal, neurological, immune, hepatic, renal, urological disorders, severe injury, or cancer that, in the opinion of the investigator, would potentially put the candidate at risk.Blood or plasmaThose with any medical contraindication (medical condition or medication) to blood donation, according to Red Cross GuidelinesThose who donated blood or plasma in the past 3 monthsThose knowing they have a condition indicative of levels of hemoglobin, hematocrit, red blood cells, or iron below the lower limit of normal levelsZone 2Currently participating in zone 2 physical activityCurrently participating in more than 120 minutes per week of aerobic, and cardiovascular training (eg, jogging, cycling, walking, swimming, high-intensity interval training) at >60% of their max heart rate.Intermittent fastingThose with a history or diagnosis of diabetes, hypoglycemia thyroid disease, or an eating disorderThose who recently participated in intermittent fasting or Time Restricted EatingThose who recently used antidiabetic medication such as Semaglutide (sold as Ozempic, Wegovy, and Rybelsus) or Tirzepatide (sold as Mounjaro) for the treatment of type 2 diabetes or weight loss will also be excluded from this group.Use of drugs that might affect intermittent fasting or eating behaviors

#### Interventions

Randomization groups are created at regular monthly intervals and clustered by recruitment region. Participants who have consented to participate in the study are randomized into 1 of the 4 study arms as either an intervention or control, accounting for their eligibility determined during the screening process and baseline serum PFOS concentrations. Upon enrollment into their specific group, participants are provided with instructional materials for assigned activities, activity timelines, and frequently asked questions.

Participants randomized in the blood donation or plasma donation arm include all participants with serum PFOS ≥5 ng/mL, following the previous Australian study [11], while also meeting additional study criteria outlined in Textbox 1. We also included a smaller intervention group of participants with PFOS <5 ng/mL in the plasma arm, to evaluate whether improvements in epigenetic age are independent of baseline PFOS. Participants in the blood intervention arm are expected to donate whole blood every 12 weeks for 12 months, while those in the plasma intervention are expected to donate plasma every 6 weeks for 12 months. Participants are provided with a list of donation centers in their region and acceptable types of donations (eg, whole blood donation is acceptable, but not “Power Red” or platelets). Participants go to donation centers on their own. Controls are asked to refrain from donating plasma or blood throughout the trial period.

Participants randomized into the zone 2 physical activity arm complete a Cardiopulmonary Exercise Test (CPET) before starting their intervention. The CPET uses a mouthpiece and external sensors to measure the heart rate and other cardiovascular health indicators of the individual while they engage in mild exercise on a stationary bicycle. The initial CPET provides a baseline evaluation of cardiovascular fitness, as well as the zone 2 heart rate zone used for the intervention. The calculated range from this exam is provided to participants in their results and they are asked to self-report these results to the study team. The zone 2 heart rate range was based on current American College of Sports Medicine guidelines and corresponded to a lower limit of 40% and an upper limit of 60% of achieved peak VO2 to indicate the anaerobic threshold [23]. Functionally, engaging in zone 2 translates to moderate physical activity, with examples of zone 2 physical activity including hiking up a hill, a light jog, or a moderate cycling session. Participants in the intervention are asked to complete a minimum of 45 minutes of physical activity in their zone 2 range for at least 4 days a week, tracked by a study-provided heart rate monitor watch. Controls are permitted to continue their regular physical activity regimen but are asked to not intentionally engage in zone 2 activity. All participants randomized to the zone 2 physical activity arm are provided with a wrist-worn accelerometer (Garmin Forerunner 45) to passively record their physical activity and sleep data. They are reminded to always wear the device except when it is charging and receive regular compliance checkups from study staff. Participants are also reminded to open the application on their phones at least once a week to allow data to be uploaded to their Garmin account. This data is synced with Fitabase to allow the study team to monitor adherence. Participants in the zone 2 physical activity arm are monitored for compliance through Fitabase and can manually report exercises if they do not wear their wrist-worn heart tracker [24]. At the end of the 4-month period, participants complete a final CPET exam and share their results with the study team to evaluate changes over time.

Participants randomized into the intermittent fasting arm are asked to fast for 14 to 16 hours per day, for at least 4 days a week for the 4-month period. Participants select their own time windows to accommodate firefighter shift schedules. During fasting windows, participants are allowed to consume medications and zero-calorie beverages (eg, black coffee, sparkling water, unsweetened tea). They are not asked to alter their diet in any other manner. Controls are asked to not engage in intermittent fasting throughout the trial period and continue their current dietary regimen. Additional details are provided in Textbox 2.

Description of study interventions within the firefighter collaborative research project.

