At enrollment and their end-of-study visit, all participants provide biological specimens (blood and urine), and a survey is administered to collect information on occupational history and exposures, relevant medical history, sleep quality, physical activity information, a food frequency questionnaire, the Center for Epidemiological Studies Depression scale (short form), and environmental exposures (Table 1, and described further in the Outcomes section). Throughout their enrollment period, all participants also receive regular study adherence questionnaires (described below). At end-of-study only, all participants additionally take a cognitive assessment (MindCrowd, described below). Participants assigned to the zone 2 physical activity arm complete a CPET before the beginning of the 4-month intervention and again after the conclusion of the intervention. Once participants in the zone 2 physical activity arm report the results of their first CPET, they are sent a wrist-worn accelerometer (Garmin Forerunner 45) that they are instructed to wear throughout the 4-month period and to return upon completion.

Zone 2 wears their accelerometer every day for the duration of the trial.

**Table 1 table1:** Participant data collection time points for participants enrolled in the firefighter collaborative research project.

	Baseline	Mid-intervention	End of study^a^
Blood	All	BP^b^	All
Urine	All	BP	All
Questionnaires^c^	All	BP	All
Adherence^d^	N/A^e^	All^f^	N/A
Cardiopulmonary Exercise Test	Z2^g^	N/A	Z2
MindCrowd cognitive assessment (verbal cognition, processing speed)	N/A	N/A	All
Accelerometer	Z2	Z2	Z2
Epigenetics (Infinium MethylationEPIC v2.0 BeadChip)	All	N/A	All
VO2max, resting heart rate, HRV^h^, HR^i^ recovery	Z2	Z2	Z2
Sleep quality (accelerometer): deep, REM^j^, light	Z2	Z2	Z2
Sleep quality (National Health Interview Survey Questionnaire): hours, rested, interruptions	All	N/A	All
Depression (CES-D^k^ Short form)	All	N/A	All
Firefighter gear and occupational exposures	All	N/A	All
Dietary quality	All	N/A	All
Self-reported weight	All	All	All

^a^End of the study is approximately 4 months after randomization for zone 2 and intermittent fasting and approximately one year for blood or plasma.

^b^BP: blood/plasma arm.

^c^Questionnaires include diet, depression or mood, physical activity, occupational characteristics, and lifestyle.

^d^Intervention adherence questionnaires are evaluated weekly for IF and Z2, and monthly for blood or plasma.

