#### Biological Specimens

All participants provide up to 50 mL of blood via venipuncture at baseline as part of the study screening process and at the completion of assigned study arm activities. Participants in the blood and plasma arm complete an additional collection at mid-study, between 4 and 8 months. Each venipuncture is performed by qualified study staff, phlebotomists, nurses, or paramedic-EMTs at organized study events hosted at participating fire stations or facilities. Upon collection, blood specimens are stored locally in coolers with ice packs for transportation to the University of Arizona, where they are processed within 24 hours, with aliquots stored at –80 °C before testing. Baseline blood specimens for all participants are analyzed for PFAS as the final step in the study screening process and for markers of epigenetic age, such as DNA methylation patterns. At the end of assigned activities, only participants in the blood and plasma arm will have their blood specimens analyzed for PFAS. All blood specimens collected at the end of assigned activities for all study arms will be analyzed for markers of epigenetic age.

Participants are asked to self-collect approximately 80 mL of urine at baseline as part of the study screening process and at the completion of assigned study arm activities per FFCCS protocol and to be stored for future analyses. Participants in the blood and plasma arms complete an additional collection at mid-study, between 4 and 8 months. Collections take place at organized study events hosted at participating fire stations or facilities. Upon collection, urine specimens are locally stored on dry ice for transportation to the University of Arizona, where specific gravity is measured using the Atago Refractometer (Model PAL-10S, Cat# 4410, Fisher Scientific). The sample is aliquoted and prepared for long-term storage at –80 °C for potential future analyses associated with these interventions.

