#### Adherence to Study Activities and Retention

To determine activity adherence, participants are contacted at regular intervals determined by their intervention via email or secure SMS test messages using Twilio. Each survey asks if the participant has completed their required study activities. Participants randomized to an intervention are asked detailed questions about completing their activities, and participants randomized to control are asked if they engaged in the intervention activities since the last study survey. During the check-in surveys, participants are able to report any adverse events. They will then be contacted by study coordinators, and the events will be reported to the IRB for review to determine any necessary actions to take.

Study coordinators call and email noncompliant participants each week to improve adherence. Participants are contacted if they are due to start study activities but have not completed their baseline survey, have at least 1 week past due for a blood or plasma donation, have not completed a weekly survey for zone 2 physical activity or intermittent fasting in 2 weeks, or have not scheduled an appointment for a follow-up biological collection. Participants may also be contacted if they do not sync their wrist-worn accelerometer (Garmin Forerunner 45) with their mobile application, or if they do not share the results of their CPET with the study team. If the participant does not respond and continues to fall behind on study activities, then the IRB-approved liaison for their department is contacted to engage with the participant and ensure they complete their activities.

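### In the zone 2 arm, the baseline exercise test and all watch data are collected after randomisation to intervention or control, so the fitness baseline is open to knowledge of allocation

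*Protocol article*

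**What the plan says.** **Allocation.** Under Interventions, consenting participants are "randomized into 1 of the 4 study arms as either an intervention or control", so arm and group are set together. The same section continues: "Upon enrollment into their specific group, participants are provided with instructional materials for assigned activities, activity timelines, and frequently asked questions".

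**Exercise test (CPET).** "Participants randomized into the zone 2 physical activity arm complete a Cardiopulmonary Exercise Test (CPET) before starting their intervention". Textbox 2 lists a first CPET under the zone 2 control group as well as the intervention group. The test's role is stated: "The initial CPET provides a baseline evaluation of cardiovascular fitness". It is repeated at 4 months so that change can be assessed. The Introduction makes cardiovascular risk reduction a primary outcome for the zone 2 arm, and Outcomes lists peak VO2 among the CPET measures.

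**Watch.** Data Management: "Once participants in the zone 2 physical activity arm report the results of their first CPET, they are sent a wrist-worn accelerometer". Table 1 nevertheless marks accelerometer, VO2max, resting heart rate, heart rate variability and watch-based sleep as baseline measures for zone 2.

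**Survey.** It is planned at enrolment: "At enrollment and their end-of-study visit, all participants provide biological specimens (blood and urine), and a survey is administered". The adherence section provides for late responders: "Participants are contacted if they are due to start study activities but have not completed their baseline survey".

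**Blood.** "Baseline blood specimens for all participants are analyzed for PFAS as the final step in the study screening process". These samples therefore precede randomisation.

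**The concern.** Participants cannot be blinded to these interventions, so the only time a zone 2 measurement can be free of knowledge of allocation is before status is disclosed. The described sequence gives up that protection for a primary outcome.

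Peak VO2 depends on how hard the participant works. Someone who knows they are about to train, or knows they are a control, may try more or less hard at the first test. A group difference arising this way is not a chance imbalance of the kind randomisation accounts for. It passes in full into a difference in change scores, and in part into a baseline-adjusted estimate.

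The watch has a related but different problem. No wear period before allocation is described and no run-in is stated, so values labelled baseline may overlap the first days of the intervention. Resting heart rate, heart rate variability and watch sleep are recorded passively and are neither effort-dependent nor self-rated. For these, the issue is the overlap, not effort.

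A survey completed late can be answered with status known, which exposes the self-rated depression and sleep items for those participants.

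**Working it through.** **Order of events in zone 2**

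1. Blood, urine and the planned survey at enrolment or screening.
2. One randomisation to arm and to intervention or control.
3. Materials for the assigned activities.
4. First CPET, in both groups.
5. CPET result reported by the participant.
6. Watch sent.
7. Assigned activities; the survey may still be outstanding when these are due.

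Steps 2, 4, 5 and 6 are fixed by the text. That step 3 comes before step 4 is an inference: the article does not time disclosure against the CPET. Nothing contradicts it, and no step that withholds group status until baseline is complete is described.

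**The plan's own figure.** No sample size for CPET is given. The stated 141 per group is for epigenetic age (difference 1 year, SD 3). Assuming two-sided 5% and 80% power, 2 × 3² × (1.960 + 0.842)² = 141.3, so it reproduces. It has no bearing on this point; only the target of 150 per zone 2 group is used below.

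**Illustration.** Assumptions, none of them from the documents: correlation ρ = 0.7 between baseline and follow-up, equal SDs, no true effect, and a group difference b (in SD units) caused by knowledge of allocation.

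- SE, change score: √(2(1 − ρ) × 2/150) = √(0.6 × 0.01333) = 0.0894
- SE, baseline-adjusted: √((1 − ρ²) × 2/150) = √(0.51 × 0.01333) = 0.0825
- Two-sided rejection rate: Φ(−1.96 + d) + Φ(−1.96 − d), where d = bias/SE

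*Shift at baseline only.* The absolute bias is b for change scores and ρb with adjustment. For b = 0.1: d = 0.1/0.0894 = 1.12, giving 20%; and d = 0.07/0.0825 = 0.85, giving 14%.

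| b (SD) | Change score | Baseline-adjusted |
|---|---|---|
| 0.05 | 9% | 7% |
| 0.1 | 20% | 14% |
| 0.2 | 61% | 40% |

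With b = 0.1, the pair is 14% and 8% at ρ = 0.5, and 49% and 43% at ρ = 0.9.

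*Same shift at baseline and follow-up.* The change-score bias is b − b = 0, giving 5%. The adjusted bias is (1 − ρ)b = 0.03, d = 0.03/0.0825 = 0.36, giving about 6.5%.

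*Shift at follow-up only (clean baseline, follow-up effort affected).* The bias is b either way. For b = 0.1: 20% for change scores; d = 0.1/0.0825 = 1.21, giving 23% with adjustment.

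*End-of-study values alone.* SE = √(2/150) = 0.1155. A baseline shift cannot enter. A follow-up shift of 0.1 gives d = 0.87 and 14%. The SE is 0.1155/0.0894 = 1.29 times that of the change score and 0.1155/0.0825 = 1.40 times that of the adjusted analysis.

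**The case against.** **Disclosure timing is inferred.** This is a condensed article, and the notification workflow could sit in a fuller protocol. That stands as a reason to write very probably, not certainly. It does not alter the stated order of randomisation, CPET and watch.

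**The shift may persist.** Follow-up is also unblinded. If the same effort difference is present at both tests, it cancels in the change score, and moving baseline ahead of disclosure would expose the follow-up difference instead. This stands. A reader might infer that any baseline shift inflates the effect one for one, or that reordering restores a 5% error rate. The first holds only for change scores with a shift that has gone by follow-up; the second holds only if follow-up effort is unaffected.

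**The analysis is not fixed as a change score for fitness.** The wording on mean differences in change is in the PFAS paragraph of Data Analysis. Fitness gets mixed models of group differences, with similar models for zone 2, and watch VO2 is to be followed as a progression over time. This stands in part, but the two CPETs are explicitly paired to assess change, so the first one matters under any model that uses it.

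**The survey is planned at enrolment.** A reader might infer that self-rated baselines are compromised throughout. The text shows only that overdue surveys are chased, and gives no count.

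**Arm-dependent skipping of the CPET.** A reader might infer that controls drop out at this step. The article says staff pursue unshared results and offers no sign of a difference by group.

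**Conclusion.** The point holds for the zone 2 arm. The baseline CPET for a primary outcome follows randomisation in both groups, very probably with status known, and the watch measures labelled baseline have no period before allocation. Baseline peak VO2 can therefore differ by group for reasons other than chance and bias the estimated change.

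Size and direction cannot be determined from the documents. The 20% and 14% figures depend on an assumed 0.1 SD shift, an assumed correlation of 0.7 and a shift absent at follow-up; if it persists, the rates are about 5% and 6.5%. They show that a small shift could matter, not that one occurred.

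Overdue surveys carry the same risk for those participants only. The documents do not support extending the point to the whole trial: PFAS and epigenetic baselines come from screening blood, and MindCrowd has no baseline.

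**What to change.** **Participants already randomised.** Results states that enrolment ended in November 2024 and that analysis had yet to begin, so this is the main usable remedy.

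- Record for each participant the date status was disclosed and the dates of the first CPET, first watch data and baseline survey.
- Add an intention-to-treat sensitivity analysis comparing end-of-study CPET and watch values between groups without the post-disclosure baseline. Randomisation supports this comparison and it needs no new data. The cost is precision (SE about 1.3 to 1.4 times larger under the assumptions above), and it does not remove any effect of knowing allocation at follow-up.
- For late surveys, use the end-of-study values and keep those participants in the analysis, again with some loss of precision.
- Relabel the watch entries in Table 1 as first post-randomisation values, and state the order of disclosure and CPET in Interventions.

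**Anyone not yet notified, and any reuse of the design.** Disclose only the arm; complete the survey, the CPET and a short watch run-in; then release intervention or control status. Both zone 2 groups already do all three, so no new test is needed. The cost is a delayed start that must cover CPET scheduling, reporting of the result and sending the watch, possibly more than a week.
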